### Statistical analysis plan

#### Power and sample size considerations

This trial is designed to be an exploratory, hypothesis-generating randomized controlled trial. Given the exploratory nature of this three-arm trial, a sample size of 60 participants (20 per group) was selected for this trial to balance feasibility with the ability to detect preliminary signals across intervention arms. Power analyses were conducted via simulation for linear mixed-effects models (LMMs) using estimated parameters relevant to repeated cognitive and biomarker outcomes measured at two time points (baseline (week 0) and 8 weeks). Assuming a moderate effect size (Cohen’s *f*^2^ = 0.25), *α* = 0.05, a compound symmetry covariance structure, and no attrition, this sample size yields approximately 60–65% power to detect a significant group × time interaction. While this power is modest, it is sufficient to estimate effect sizes with reasonable precision and assess trends across intervention arms. Since LMMs maximize available data and accommodate unbalanced designs and missing data, LMMs are preferred over repeated measures ANOVA for small-sample trials with incomplete follow-up. Results from this study will guide power calculations and design refinements for a fully powered randomized controlled trial. As generally recommended for early-phase behavioral intervention studies, this trial’s emphasis will be placed on effect sizes and confidence intervals instead of solely statistical significance.

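### The stated 60–65% power does not follow from the stated effect size f² = 0.25; the effect size and the power need to be reconciled

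*Protocol article*

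**What the plan says.** Under Power and sample size considerations the article says that "a sample size of 60 participants (20 per group) was selected for this trial", as a balance between feasibility and the ability to detect preliminary signals. Power was simulated for linear mixed-effects models of "repeated cognitive and biomarker outcomes measured at two time points (baseline (week 0) and 8 weeks"). The stated inputs are: "Assuming a moderate effect size (Cohen’s *f*^2^ = 0.25), *α* = 0.05, a compound symmetry covariance structure, and no attrition". The stated result is that "this sample size yields approximately 60–65% power to detect a significant group × time interaction". The article calls this power modest. It gives neither the correlation between visits nor the variance to which the effect size refers.

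The Analysis plan section gives the model: fixed effects for group, time and group × time, with a random intercept per subject to account for correlation within a person over time. It makes the group × time term the main test of efficacy.

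**The concern.** The article prints both the inputs and the result of a power calculation, so the result can be checked. An f² of 0.25 is f = 0.5, which by convention is a large effect and not a moderate one; 0.25 is the conventional medium value of f. With 60 participants, an effect of f = 0.5 would normally be detected with much more than 60–65% power. Either the effect size or the power therefore appears to be misprinted or miscalculated.

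What is at stake is how the trial is read. A reader cannot tell whether it has good power for a large effect, modest power for a moderate one, or poor power for a moderate one. A colleague planning the follow-on trial who took over the printed pair of figures would start from an effect size and a power that do not belong together.

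**Working it through.** **Inputs from the article.** N = 60 in three arms of 20; two time points; α = 0.05; compound symmetry; no attrition; f² = 0.25; test of group × time.

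**Not given in the article, so varied here.** The correlation ρ between baseline and week 8 (taken as 0 or more, as a random intercept implies), and the variance scale of the effect size.

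**Reduction of the test.** With two visits, complete data and equal arms, the group × time test is the one-way ANOVA F test on change scores. Numerator df = 3 − 1 = 2, error df = 60 − 3 = 57, and the 5% critical value is 3.16. Power is the probability that a noncentral F(2, 57, λ) exceeds 3.16. The scale on which f² is defined sets λ.

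**Attempt to reproduce 60–65% with f² = 0.25**

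| Scale of f² | λ | Power |
|---|---|---|
| SD of change, λ = N·f² | 60 × 0.25 = 15 | 93.2% |
| Observation level, λ = 2N·f² | 120 × 0.25 = 30 | 99.9% |
| Within-between convention, λ = 2N·f²/(1 − ρ) | 30 or more | 99.9% or more |
| Raw follow-up SD, λ = N·f²/(2(1 − ρ)), ρ = 0 | 15/2 = 7.5 | 66.3% |
| Same, ρ = 0.3 | 15/1.4 = 10.7 | 82.2% |
| Same, ρ = 0.5 | 15/1 = 15 | 93.2% |
| Same, ρ = 0.7 | 15/0.6 = 25 | 99.5% |

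None of these falls within 60–65%. The nearest is 66.3%, on the raw follow-up SD with zero correlation. A simulation of the change-scale case (20,000 replicates) gave 93%, in agreement with the formula.

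**Working back from the stated power.** Power of 60% needs λ = 6.55 and power of 65% needs λ = 7.29. On the change scale, f² = λ/60, so f² = 0.109 to 0.122 (f = 0.33 to 0.35). That is less than half the stated f².

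**If f = 0.25 was meant (f² = 0.0625)**

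| Scale | λ | Power |
|---|---|---|
| SD of change | 60 × 0.0625 = 3.75 | 37.4% |
| Within-between convention, ρ = 0 | 120 × 0.0625 = 7.5 | 66.3% |
| Within-between convention, ρ = 0.5 | 7.5/0.5 = 15 | 93.2% |
| Raw follow-up SD, ρ = 0 | 3.75/2 = 1.88 | 20.5% |
| Raw follow-up SD, ρ = 0.5 | 3.75/1 = 3.75 | 37.4% |
| Raw follow-up SD, ρ = 0.72 | 3.75/0.56 = 6.70 | 61.0% |
| Raw follow-up SD, ρ = 0.74 | 3.75/0.52 = 7.21 | 64.5% |
| Raw follow-up SD, ρ = 0.8 | 3.75/0.4 = 9.38 | 76.5% |

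The stated power is thus recovered with f = 0.25 on the raw follow-up SD at ρ of about 0.71 to 0.74.

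**The case against.** The strongest reply is that the power came from simulation, and that a condensed article may leave the correlation and the variance scale to a fuller document. That stands as far as it goes: the absence of ρ is not in itself a fault. It does not remove the conflict, because with f² = 0.25 no value of ρ from 0 upwards gives 60–65% on any of the scales tried. Nor does simulation explain the gap, since the scenario is balanced and complete and the F result is exact under normality.

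Four stronger readings are tempting, and the document does not support them.

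- *That the stated pair is impossible, with power at least 93% on every definition.* On the raw follow-up SD with ρ below 0.5, power lies between 66% and 93%. Zero correlation is a limiting case of compound symmetry. It is implausible for repeated measures and sits badly with a random intercept, but it is not excluded.
- *That the true power is 37%.* This needs two guesses: that f was meant, and that the scale is change. With f = 0.25 on the raw follow-up SD and a plausible correlation, the printed power may be right and only the exponent wrong.
- *That the sample size rests on this figure.* The article says that 60 was chosen to balance feasibility with signal detection, and that the trial's results, not this planning figure, will guide later power calculations.
- *That zero attrition is an error, or that the precision claim fails.* Zero attrition is openly declared as the scenario, and planning for missing data does not contradict it. The article also says of its power that "it is sufficient to estimate effect sizes with reasonable precision and assess trends across intervention arms", but sets no precision threshold that could be failed. It claims no power for the comparison of participants with and without mild cognitive impairment.

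**Conclusion.** The concern holds as an inconsistency between two printed figures. As written, f² = 0.25 gives 93% power on the change scale and over 99% at observation level, against the stated 60–65%. The closest alternative gives 66% and requires zero correlation between visits. Across all the readings examined, for f or f², power runs from about 20% to over 99%, so the paragraph does not tell the reader what the trial can detect.

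The document does not show which figure is wrong. The word moderate points to f having been meant, but that is an inference. The result assumes normal outcomes, equal arms, complete data and ρ of 0 or more. No analysis, sample size or decision rule depends on the figure.

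**What to change.** Rerun the calculation and rewrite the sentence so that it names:

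- whether the effect size is f or f²;
- the variance to which it refers (SD of change, raw follow-up SD or observation-level residual);
- the assumed correlation between baseline and week 8.

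Then correct whichever of the effect size or the power is wrong, so that the two agree, and make the word moderate fit the value kept. If the simulation did use f = 0.25 on the raw follow-up SD with a correlation near 0.72–0.74, correcting the symbol and adding those two inputs is enough.

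The cost is a few lines of text and one changed figure. Sample size, procedures and analysis stay as they are.

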#### Analysis plan

This study is designed as a three-arm, parallel-group trial comparing the effects of an 8-week exercise intervention (group 1), sleep intervention (group 2), and combined sleep + exercise intervention (group 3) on cognitive performance and biomarkers for brain and cardiometabolic health in older adults with MCI or no cognitive impairment. A total of 60 participants (20 per group) will be enrolled. All analyses will be conducted using IBM SPSS Statistics (Version 31.0.0.0; IBM Corp., Armonk, NY, USA). The primary analytic goal is to determine which intervention arm may demonstrate the greatest improvements in cognitive function and biomarker profiles. Descriptive statistics (means, standard deviations, medians, interquartile ranges, and proportions) will be used to summarize demographic characteristics, intervention adherence, and baseline measures. Primary outcomes will include change**s** in cognitive domain-specific and global cognition scores from the digital cognitive assessments and changes in biomarkers for brain (NfL) and cardiometabolic health (HbA1c, hs-CRP, C-peptide, insulin, total cholesterol, HDL, LDL, triglycerides). Secondary outcomes will include changes in sleep metrics (e.g., sleep efficiency, SWS, REM sleep, and total sleep durations, onset latency, and restlessness, as measured via Elemind) and physical activity/exercise levels (PGE and NPA via Fitbit). Tertiary outcomes will include the role of light exposure (measured via Lys) as a potential modulator of sleep parameters and psychosocial measures (e.g., PROMIS Depression, Social Isolation).

Primary group comparisons will be conducted using LMMs, which offer flexibility for handling repeated measures, unbalanced data, and missingness under the Missing at Random assumption. Each LMM will include fixed effects for group (sleep, exercise, combined sleep + exercise), time (baseline, 8-week follow-up), and the interaction term between group × time. Subject-specific random intercepts will be included to account for intra-individual correlation over time. The main test of intervention efficacy will be the group × time interaction term. To evaluate whether improvements in biomarkers (e.g., HbA1c, hs-CRP) moderate the effects of the interventions on cognitive outcomes, exploratory moderation models will be conducted. These models will include biomarker change scores, group assignment, and group × biomarker interaction terms as predictors of cognitive change. Moderation models will use PROCESS v5.0 Macro for SPSS with bias-corrected bootstrapping (5,000 resamples). Significant interactions will be probed using Johnson-Neyman techniques.

Given the small sample size, power for detecting small effects will be limited. Thus, all models will report estimated effect sizes (Cohen’s *d*, partial *η*^2^), 95% confidence intervals, and significance levels (*α* = 0.05). No corrections for multiple comparisons will be applied to primary outcomes; however, for secondary and exploratory outcomes, a Benjamini–Hochberg false discovery rate (FDR) correction will be used to control for Type I error. Composite indices may be created to reduce variable dimensionality. For cognitive outcomes, domain-specific cognitive function scores will be z-scored and aggregated into a global composite score. For blood-based biomarkers, z-scored values will be averaged to create an overall plasma-based AD risk index as well as a cardiometabolic risk index for all subjects.

Missing data will be handled using maximum likelihood estimation within LMMs. For summary scores or self-report questionnaires with partially missing responses, scale-specific rules will be applied, if available. Participants missing more than 2 weeks of intervention or follow-up cognitive assessments will be excluded from per-protocol models but retained in intention-to-treat analyses. Missingness patterns will be analyzed and classified as Missing Completely at Random (MCAR), Missing at Random (MAR), or Missing Not at Random (MNAR). All assumptions for normality, linearity, and homoscedasticity will be checked using residual plots and Kolmogorov–Smirnov tests. Skewed variables (e.g., hs-CRP) will be square root- or log-transformed prior to modeling. Outliers will be identified using leverage and Cook’s distance, and sensitivity analyses will be performed with and without influential points.

As an alternative analytic strategy, if models fail to yield significant results due to insufficient power or high variability, effect sizes and confidence intervals (CIs) will be emphasized. A simplified analysis approach using ANCOVA (controlling for baseline scores) will be explored for key outcomes. Lastly, pattern mixture modeling may be used to examine intervention effects under different missing data assumptions.

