### Interventional group 1 (exercise only)

Participants randomized to the exercise-only group will engage in an 8-week, home- and site-based exercise intervention designed for older adults across a range of cognitive and physical function levels. All site-based sessions will occur in-person at the study facility under supervision of trained staff. Each week, participants will attend two 60-minute structured exercise sessions, consisting of aerobic training and resistance training. On the remaining five days when subjects will not engage in structured exercise, subjects will be asked to engage in 30 minutes of moderate-intensity walking activities. In-lab exercise protocols will be fully standardized to ensure consistency of exercise dosage and fidelity across participants. The target exercise load will be 270 minutes of moderate-intensity exercise weekly for 8 weeks. Although considered short-term exercise, this exercise dosage has been shown to improve cerebral blood flow, regional brain volume, and brain-protective trophic factors [32].

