Participants will begin with a 7-day onboarding period, during which participants will wear the Fitbit continuously to establish baseline physical activity levels and to ensure initial eligibility criteria are satisfied. Subsequent to this initial observation and screening phase, subjects will participate in biweekly, in-person exercise sessions, which will be comprised of 60 minutes of stretching, aerobic, and resistance training exercises. Specifically, exercise sessions will consist of a 10-minute warm-up, followed by 20 minutes of moderate-intensity aerobic exercise at 60–75% of estimated maximum heart rate (MHR). MHR will be estimated using Tanaka’s formula (maxHR = 208-(0.7*age)) [33], and the target heart rate (THR) will be calculated using Karvonen’s formula to account for resting heart rate (RHR), where THR = ((MHR-RHR)*% intensity) + RHR [34]. Moderate-intensity aerobic training will be followed by 20 minutes of resistance training of major muscle groups with an emphasis on lower extremity resistance training one day each week and upper extremity resistance training at the second in-person session weekly. Exercise load will be at 60–80% of an estimated one repetition max using American College of Sports Medicine Guidelines [35]. Muscle groups that will be trained include biceps, triceps, deltoid, and latissimus dorsi for the upper extremity, and quadriceps, hamstrings, and gastrocnemius/soleus for the lower extremity. Resistance training exercises targeting the trunk will also be incorporated. Each exercise session will then conclude with 10 minutes of post-exercise stretching.

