#### Continuous physical activity monitoring

Participants will wear a Fitbit continuously throughout the study, including during both wake and sleep hours. Fitbit-derived data will be categorized into three activity domains:Protocol-Guided Exercise (PGE): Exercise occurring during supervised, in-lab sessions.Non-Protocol Physical Activity (NPA): Incidental movement and unsupervised activity outside scheduled sessions.Total Physical Activity: Combined PGE + NPA, derived from 24-h Fitbit data.

The primary Fitbit metric will be daily step count, a validated proxy for global movement shown to correlate with cognitive, brain, and cardiometabolic health outcomes in older adults [37]. A secondary metric, calories burned, will offer insight into the metabolic intensity of movement. Step count and caloric expenditure will be examined in relation to cognitive function as well as brain and cardiometabolic biomarker outcomes. Analytical models will include PGE and NPA as independent predictors, which will be modeled separately and jointly to assess differential and additive contributions to primary (cognitive, brain, and cardiometabolic markers), secondary (sleep metrics and exercise measures), and tertiary (light exposure and psychosocial measures) outcomes.

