#### Device use and sleep monitoring

Subjects will start with a 7-day onboarding-screening period, during which participants will wear the Elemind Neuromodulation headband nightly without stimulation to passively establish a baseline sleep pattern and to ensure initial eligibility criteria are satisfied. Following this, the neuromodulation feature will be activated, and participants will be instructed to wear the device at least 3–4 nights per week for 8 weeks. Each use will deliver bone-conduction-based acoustic stimulation tailored to the participant’s real-time brainwave activity. The headband will collect continuous data on multiple sleep metrics, including total sleep time, sleep efficiency, sleep onset latency, restlessness, and time spent in various sleep stages (light (N1/N2), N3, REM). Sleep data will be delivered to the Elemind smartphone application. Raw data will be reviewed regularly for artifacts, such as signal dropout and excessive motion. Nights with incomplete data (e.g., < 4 hours of recording or ≥ 10% missing epochs) will be flagged and excluded from analysis and will prompt follow-up instructions and/or re-onboarding support. The Elemind Neuromodulation device’s sleep staging outputs, while designed to approximate polysomnographic benchmarks, are considered proxies and will be interpreted accordingly. In addition, participants will wear the Lys device continuously throughout the 8-week trial period. The Lys device will measure the intensity, color, and duration of light exposure to gain insights into the relationship between light, sleep, circadian cycles, and energy levels. This device works by communicating with the company’s proprietary app, named Insight, to display light exposure data to the user as well as to provide the individual with goals and insights related to light and health. Additionally, Lys communicates with a separate app, called Collect, which will be used by the researchers to download data at the conclusion of the study. In addition, subjects in this group will also receive Fitbit devices and will be asked to wear the device continuously to passively gauge physical activity levels throughout the trial duration.

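### Change in PGE is listed as a secondary activity outcome, but PGE is zero by definition at baseline and throughout the sleep-only arm, so it measures adherence or dose rather than an effect on activity

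*Protocol article*

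**What the plan says.** The section Continuous physical activity monitoring splits Fitbit data into three domains. The first is "Protocol-Guided Exercise (PGE): Exercise occurring during supervised, in-lab sessions". The second, NPA, is movement outside scheduled sessions. The third, Total Physical Activity, is "Combined PGE + NPA, derived from 24-h Fitbit data". Daily step count is named as the primary Fitbit metric. The same section states that "Analytical models will include PGE and NPA as independent predictors", with secondary outcomes (sleep metrics and exercise measures) among the outcomes to be modelled.

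The Analysis plan then names change in "physical activity/exercise levels (PGE and NPA via Fitbit" as secondary outcomes. Total Physical Activity is not named there.

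On who can have any PGE and when:
- Exercise-only: "Subsequent to this initial observation and screening phase, subjects will participate in biweekly, in-person exercise sessions". The planned dose is "Each week, participants will attend two 60-minute structured exercise sessions, consisting of aerobic training and resistance training". The combined arm follows the same cadence (Protocol structure and considerations).
- Sleep-only: the intervention is the headband. For the Fitbit, participants are "asked to wear the device continuously to passively gauge physical activity levels throughout the trial duration" (Device use and sleep monitoring). No in-lab exercise session is scheduled.

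The Analysis plan makes the group × time term (baseline, week 8) the main test of efficacy. On multiplicity, "for secondary and exploratory outcomes, a Benjamini–Hochberg false discovery rate (FDR) correction will be used". PGE is exempted from neither.

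**The concern.** A variable that can be non-zero only after the start of the intervention, and only in two of three arms, cannot show whether an intervention changed how active people are. Someone who attends every session and cuts other movement by the same amount has a positive change in PGE and no change in activity. A significant group × time result for PGE would nevertheless appear under the label of physical activity or exercise level. The plan's emphasis on effect sizes does not help, because a PGE effect size is set by assignment and attendance in the same way.

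There are two side effects. A near-certain rejection in a Benjamini–Hochberg family relaxes the cut-offs for the informative outcomes in it. And one arm has no variance, which a model with a common residual variance cannot accommodate.

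**Working it through.** The plan gives no figure for PGE, so there is none to reproduce.

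**1. Structure.** From the definition and the schedule:

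| Arm | PGE at baseline | PGE at week 8 | Change |
|---|---|---|---|
| Exercise-only | 0 | sessions attended | ≥ 0 |
| Sleep-only | 0 | 0 | exactly 0 |
| Combined | 0 | sessions attended | ≥ 0 |

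**2. Behaviour of the test.** With two balanced time points and random intercepts, the group × time test is a one-way ANOVA on change (2 and 57 df for 20 per arm). It was simulated with no arm difference in total activity. Assumed inputs, not in the protocol: two week-8 sessions, each attended independently; 2,500 steps per session (SD 800); SD of change in total activity 1,500 steps/day; 3,000 runs per row.

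| Attendance | PGE significant | NPA significant | Total significant |
|---|---|---|---|
| 100% | 100% | 31% | 4.9% |
| 80% | 100% | 21% | 4.7% |
| 50% | 100% | 11% | 4.4% |
| 30% | 99.9% | 6.5% | 5.3% |
| 20% | 91% | 5.6% | 5.1% |
| 10% | 32% | 5.2% | 5.0% |
| 5% | 10% | 5.1% | 5.0% |

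A separate simulation, also using only the week-8 sessions, gave 95%, 38% and 12% at 20%, 10% and 5% attendance. Averaging over all 16 sessions instead gives 100% at 20%.

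**3. Variance.** If each exercise arm has SD s for change in PGE and sleep-only has 0, the pooled variance is (s² + 0 + s²)/3 = 2s²/3. For exercise-only against combined, the standard error is then √(2/3) = 0.82 of its proper size, so the interval is too narrow.

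**4. Benjamini–Hochberg cut-offs.** Take q = 0.05 and m = 8 (the six named sleep metrics, PGE, NPA). If PGE is certain to be rejected, the k-th smallest of the other seven p-values is compared with 0.05(k+1)/8. Without PGE in the family it is compared with 0.05k/7:

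| k | Without PGE | With PGE |
|---|---|---|
| 1 | 0.0071 | 0.0125 |
| 2 | 0.0143 | 0.0188 |
| 3 | 0.0214 | 0.0250 |
| 7 | 0.0500 | 0.0500 |

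At k = 1 the cut-off is 0.0125/0.0071 = 1.75 times looser. The direction holds for any family size, since (k+1)/m ≥ k/(m−1) whenever k ≤ m−1.

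**5. Error rates when the other outcomes are all null.**
- FDR over the whole family including PGE: 0.05 × 7/8 = 4.4% (simulated 4.4%).
- Chance of any false claim among the other 7: 5.0% without PGE, 8.5% with it. At correlation 0.3 it is 4.8% and 8.0%; at 0.5, 4.4% and 7.0%.
- With 9 to 20 other outcomes: 5.0% without PGE, 8.8–9.2% with it.

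**The case against.** Several points on the other side stand.

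- **FDR control is kept.** A reader might infer that the Benjamini–Hochberg guarantee is broken. It is not: PGE truly differs between arms, and the rate over the full family is 4.4%. The rise to 8.5% is a familywise quantity that the procedure does not promise to control, and any real secondary effect would cause the same rise. Per outcome, the false-positive rate among the other seven goes only from about 0.8% to 1.3%.
- **The family is assumed.** The sleep metrics are given as examples, other cognitive functions are also secondary (Cognitive assessments), and q is not stated. An article may leave these to the full plan. The direction of the effect is unaffected.
- **The test is inferred.** The Analysis plan introduces the mixed model for primary comparisons. Its use for secondary outcomes is the natural reading but is not spelled out.
- **Significance is not unconditional.** A reader might infer that PGE is significant whatever happens. It needs some attendance; at 10% the test rejects in only about a third of trials.
- **NPA sits beside PGE** and would fall if people substituted sessions for other movement. This helps only in part: where total activity is unchanged, NPA flags the fall in 31% of trials at full attendance and 11% at 50%, while PGE is significant in all of them.
- **Circularity is one reading.** It is tempting to say that PGE and NPA are regressed on themselves. The term exercise measures could also cover the six-minute walk test, PASE or CHAMPS, for which PGE and NPA are coherent predictors. The text needs clarifying; it does not prove a circular model.
- **Zero baseline variance alone does no harm**, because the test reduces to an ANOVA on change. The arm without variance remains a problem. The planned homoscedasticity checks would flag it, but no transformation cures a constant zero.

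None of this makes change in PGE a measure of activity level.

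**Conclusion.** The point holds as one about what PGE can measure. By the protocol's own definition and schedule, its between-arm contrast is an adherence or dose contrast. Under the group × time model it would be significant almost surely at about 30% attendance or more, with no difference in total activity. That threshold rests on the assumed step counts and independent attendance; the structural zeros rest on nothing beyond the text.

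The effect on the other outcomes through the FDR correction is real but modest, and its size depends on the assumed 8 tests and q = 0.05. No primary outcome and no sample-size figure is affected. The change is worth making because it removes an uninformative result that would be read as an intervention effect, and replaces it with a question the trial can answer.

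**What to change.** 1. In the Analysis plan, make change in Total Physical Activity (24-h Fitbit daily step count, baseline and intervention, all three arms) the between-arm activity outcome. NPA may stay alongside it.
2. Report PGE descriptively, as adherence in the two exercise arms. Leave it out of the group × time tests and out of the Benjamini–Hochberg family. Adherence is already to be recorded and summarized (Adherence and engagement; Analysis strategy), so nothing is lost.
3. In Continuous physical activity monitoring, state that PGE and NPA are not used as predictors of outcomes that are themselves PGE or NPA, and say which exercise measures are meant.

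The cost is wording. Total Physical Activity is already derived, and the Fitbit is worn in every arm before and during the intervention. The price is that the activity outcome is no longer near-certain to be significant.
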